### **Baseline study**

At baseline, information on socio-economic status, vaccination status, appetite, morbidity patterns, dietary patterns, anthropometric measurements, serum zinc(zn), serum albumin and CRP of the children will be collected.

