### **Randomization**

The sampling frame will consist of the 12 villages in Kiandutu slum. Three villages will be randomly allocated to each of the 4 study groups. Villages rather than study subjects will be randomized to avoid cross-contamination of information due of the close proximity of the study subjects. Computer generated randomization will be done by a statistician.

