### **Data collection tools and procedures**

Baseline data on children's past and present illnesses will be obtained by interviewing the primary caregivers and from confirmation from health cards. A semi-structured questionnaire designed to elicit information on the household socio-economic, demographic structure, parental education and employment, material possessions and type of housing materials. A 24-hour recall designed for measuring nutrient intakes inclusive of zinc will be used and a Food Frequency Questionnaire (FFQ) will be administered to cover the most commonly consumed complementary foods based on a 7-day recall. Appetite will be assessed monthly using the Children's Eating Behaviour Questionnaire (CEBQ),

Serum zn, albumin and CRP will be determined at baseline and post-intervention. Monthly anthropometric measurements and dietary intake will be conducted monthly for the 6-month period. Interviewers will visit the childrens' homes bi-weekly to inquire about symptoms of illness (severity, frequency and duration) of diarrhoea, ARTI and other infections, and monitor the feeding practices.

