### 3.4.6 Sample size determination

Determination of sample size will be based on the primary objective and the formula by Liu

& Chow (1992). Where; 
$$n = \frac{(Z_{\alpha} + Z_{\beta})^2 \sigma^2}{(\delta - \varepsilon)^2} = \frac{(1.64 + 1.28)^2 0.71^2}{(0.2 - 1.0)^2} = 67$$

Where; n = No. of study subjects per group,  $\sigma$  = variance within the groups,  $\delta$  = expected outcome difference of the groups (20 % as per the bioequivalence rule),  $\varepsilon$  = the absolute values of proportion differences among the groups. The standard normal deviate at the required confidence interval (95 probability error).

The prevalence of zinc deficiency in Kenya is 50% (GOK & UNICEF, 2008). The estimated post-intervention prevalence of 20%, 10%, 20% and 50% for the reference, ZN, ZN in MMN and MMN without ZN groups respectively. To show equivalence within 20% rule with 80% power and 5% significance, a sample size of 67 per group was obtained and allowing 20% attrition, a sample size of 80 per group is obtained.

Where; n = The desired sample size, z = The standard normal deviate at the required confidence interval (95 probability error equal to 1.96), p = The proportion of occurrence of the phenomenon (0.5) since prevalence is 50%, q = The proportion of non-occurrence is (1-P) = 0.5, d = level of statistical significance (0.05 for 95% level of significance).

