### **Data analyses**

The field data will be cleaned and coded and analyzed using SPSS software. Socio-economic (SE) status data will be reduced by using principal components analyses to an index using STATA. ENA for SMART will be used to analyse anthropometric data. The indices used to determine nutritional status will be; WA, HA and WH. Nutritional status will be judged by the WHO standards. Child feeding practices will be assessed using the indicators as per WHO (2001b) and WHO (2007) IYCF guidelines. Child feeding index, breastfeeding and complementary feeding (initiation, meal frequency and dietary diversity as a proxy for quality) will be determined. Nutrient intakes will be analyzed using Nutri-survey. Relative risk and odds ratio will be used to show the association between morbidity patterns and zinc status. Pearson product moment correlation and chi-square will be used to determine the relationship between non-categorical variables (feeding practices and nutrition status, SE status) and categorical variables (sex, age, type of illness and maternal characteristics) with zinc status respectively.

The relationships between the categorical variables will be analyzed to assess inter-group differences in dietary practices, nutrition status, morbidity patterns and serum and hair zn status at baseline, monthly and end of the study using chi-square and t-test, ANOVA and ANCOVA. Simple linear regression will be used to determine the contribution of sprinkles/CSB, dietary practices and SE status to nutrition status, morbidity patterns and

serum zn levels. Multiple regression analysis will be used to determine the extent to which sprinkles/fortification, dietary practices and predict nutrition status, morbidity patterns and serum zn levels and logistical regression used to analyze for confounding variables. Content analysis will be used for qualitative data from FGDs by summarizing the information into emerging themes. Bioequivalence of sprinkles to CSB will be drawn if the percentages of children with serum zn  $<9.9 \mu\text{mol/L}$  is within  $\pm 20$  rule (excluding CRP levels  $>10 \text{ mg/l}$ ), the basis to accept or reject the null hypothesis. Significance will be determined at 95% confidence interval, P-value of 0.05.

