### **Logistical and ethical considerations**

Clearance will be sought from the Graduate School, Kenyatta University and a research permit obtained from the Ministry of Education. Authority to conduct research will be obtained from the Ministry of Health, Thika and the local chief. Ethical approval will be obtained from the KEMRI National Ethical Review Committee and a thumb print or written informed consent sought from the parents, after explaining the purpose of the study without revealing the study hypotheses. The food supplements will also be given to all the underfive children in the intervention households. Sick children will be advised to seek further medical attention at Thika Level 5 Hospital. Blood will be drawn two times during the study from children whose parents consent. The information provided will be treated in the strictest confidence and none of the participants will be individually identifiable in the resulting thesis and that it will be used for the purpose of the study only. The outcome of research will be communicated to the respondents.

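### The rule that decides equivalence uses no baseline serum zinc although it is planned to be measured; this costs precision and is not a bias

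*Protocol*

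**What the plan says.** - **Decision rule** (Data analyses): "Bioequivalence of sprinkles to CSB will be drawn if the percentages of children with serum zn" below 9.9 µmol/L are within the ±20 rule, leaving out CRP above 10 mg/l. This is named as the basis for accepting or rejecting the null hypothesis. The sentence names no baseline value, covariate, village term or time point.
- **Other analyses** (same section): chi-square, t-test, ANOVA and ANCOVA are listed together for group differences in several outcomes, zinc status among them, at baseline, monthly and at the end. Logistic regression is listed for confounders. Neither names baseline zinc, and neither is linked to the decision rule.
- **Measurements**: the Baseline study section includes "serum zinc(zn), serum albumin and CRP of the children will be collected". Data collection tools and procedures states "Serum zn, albumin and CRP will be determined at baseline and post-intervention". Logistical and ethical considerations adds "Blood will be drawn two times during the study from children whose parents consent".
- **Allocation** (Randomization): "Three villages will be randomly allocated to each of the 4 study groups". No stratification, matching or other restriction is described.
- **Planning figures** (3.4.6 Sample size determination): "The prevalence of zinc deficiency in Kenya is 50" per cent. "The estimated post-intervention prevalence of 20%, 10%, 20% and 50" per cent are given for the reference, zinc, zinc in multiple micronutrients, and multiple micronutrients without zinc groups. The margin is "20 % as per the bioequivalence rule"; its scale (absolute or relative) is not stated.

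**The concern.** A child's zinc level before the intervention is a natural predictor of the level six months later. The plan pays for that measurement but does not use it in the one comparison that decides the trial. With three villages per arm, chance differences in baseline deficiency between arms can be sizeable. Whatever part of them persists adds noise to a contrast that must fall within a fixed margin. In an equivalence trial, noise makes the margin harder to meet when the products really are alike. Listing adjusted analyses beside a rule that does not refer to them also leaves it open, once the data are seen, which result counts.

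**Working it through.** **Inputs from the Protocol.** 80 per group; 3 villages per group, so 80/3 = 26.7 children per village; baseline deficiency 50%; post-intervention 20% (reference), 10% (zinc), 20% (zinc in multiple micronutrients); margin 20, read as percentage points. The 80 is the plan's 67 × 1.20 = 80.4. The 67 does not follow from the printed formula: 2.92² × 0.71² / 0.8² = 6.7. That is a separate matter, and the 80 is taken here as given.

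**Assumed, because the Protocol gives neither.** ICC of 0, 0.02 or 0.05; baseline-to-end correlation of 0.3, 0.5 or 0.7.

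**1. How large is chance imbalance at baseline?** SD of the difference between two arms = √(2 × 0.25/80 × DE), with DE = 1 + (26.7 − 1) × ICC. The last column uses the normal approximation.

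| ICC | DE | SD (points) | P(difference above 10 points) |
|---|---|---|---|
| 0 | 1.00 | 7.9 | 21% |
| 0.02 | 1.51 | 9.7 | 30% |
| 0.05 | 2.28 | 11.9 | 40% |

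**2. How much of it can carry through?** Let a and b be the post-intervention risks of deficiency for children deficient and not deficient at baseline. The child-level carry-through of deficiency status is a − b. With half the children deficient at baseline, 0.5a + 0.5b equals the post-intervention rate.
- Rate 20%: a + b = 0.40, so a − b is at most 0.40, reached only if b = 0. A 10-point imbalance carries at most 4 points.
- Rate 10%: a + b = 0.20, so at most 0.20, or 2 points.

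Against 20 points these are 20% and 10% of the margin, as upper limits. In general the limit is the post-intervention rate divided by the baseline rate. It therefore does not bind in the arm without zinc, where both are 50%; but that arm is planned 30 points away from the reference (50% against 20%), outside the margin.

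**3. What does adjustment buy?** Simulation: two arms of 3 villages with 22 children each, 20% deficient in both arms, ICC 0.05 and the correlation both on an underlying normal scale, linear adjustment for continuous baseline zinc, 4,000 runs.

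| Correlation | SD unadjusted | SD adjusted | Reduction |
|---|---|---|---|
| 0.3 | 0.088 | 0.086 | 2% |
| 0.5 | 0.086 | 0.079 | 8% |
| 0.7 | 0.089 | 0.072 | 19% |

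Both estimators were centred on the true difference.

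**4. Is a village-level regression as good?** It costs one degree of freedom. With all 12 villages, 12 − 4 = 8 falls to 7, and the 90% t multiplier rises from 1.860 to 1.895 (2%). For one pair of arms, 4 falls to 3, and it rises from 2.132 to 2.353 (10%). These increases roughly cancel the gains at correlations of 0.3 and 0.5 respectively.

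**The case against.** The strongest objection is that covariates for a primary contrast usually belong in an SAP, which is not at hand, and that the Protocol nowhere forbids adjustment. That would settle the matter if the Protocol were silent on how equivalence is decided. It is not: it states the accept-or-reject basis and leaves baseline zinc out of it. The objection does stand to this extent: the plan contains no error or contradiction here, only a rule that can be improved.

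A reader might infer more than the text supports:
- *That imbalance passes straight into the result, or biases it.* Only the correlated share passes through, and over randomisation it is variance.
- *That three villages per arm cause the imbalance.* Even with no clustering, 21% of trials exceed 10 points, so more than half of the 30% to 40% is ordinary sampling variation.
- *That the Protocol prescribes raw end-of-study percentages and unrestricted allocation.* It uses none of these terms. The time point is inferred from the post-intervention rates in the sample size section, and on restriction the Protocol is simply silent.
- *That every child has a baseline value.* Blood is drawn only where parents consent.

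It is also fair to say that the gain may be small: about 2% in SD if the correlation is 0.3.

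**Conclusion.** The point holds as a recommended improvement in efficiency. The deciding rule leaves out a predictor that the trial already plans to measure, and the ANCOVA and logistic regression do not supply it because nothing ties them to the rule. Baseline imbalance above 10 points between a given pair of arms is common, but on the plan's own rates its child-level effect on the contrast is limited to 4 points (20% rate) or 2 points (10% rate).

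This rests on assumed ICCs and correlations, on a national 50% figure standing in for the baseline rate of these children, on the margin being in percentage points, and on carry-through at child level. A village-level slope could differ, and the Protocol gives no basis for one. Adjustment does not by itself deal with clustering. Nor does it repair a reading of ±20 as a rule on point estimates: in the same simulation at ICC 0.05, with a true difference of 20 points, such a rule declared equivalence in about half of trials with or without adjustment.

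**What to change.** In Data analyses, state that equivalence is judged on the post-intervention difference in the percentage of children with serum zinc below 9.9 µmol/L, as follows:
- adjusted for the child's baseline serum zinc as a continuous variable and standardised to a difference in percentage points;
- with village accounted for by a method suited to few clusters;
- with a confidence interval of stated level compared with the ±20 margin, and the margin's scale stated;
- with the unadjusted difference reported alongside.

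Say that the listed ANCOVA and logistic regression do not decide equivalence. Baseline CRP and age may be added but are optional. A regression on village percentages is not recommended, because the lost degree of freedom can offset a modest gain.

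Cost: some wording and slight modelling work, with no new blood draw or visit. The plan must also say how children with a post-intervention result but no baseline zinc value are handled.

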## **STUDY PROTOCOL**

### **Study design**

The study will adopt a cluster randomized bioequivalence trial with four study groups; zinc, zinc in multiple micronutrients and multiple micronutrients without zinc (experimental groups adding once daily Micronutrient Powders (sprinklestm) to corn-soy porridge) and a comparator group on daily conventionally fortified Corn-Soy Blend (CSB).

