### **Description of the intervention**

CSB (80% corn and 20% soy) and sprinkles meeting 100% RDA of zinc will be sourced from suppliers. For a period of six months, sprinkles (1g) will be added to corn-soy porridge once daily and CSB porridges made from 100g flour will be given daily (Figure 1). The micronutrient composition of the different study groups is shown in Table 1. The food supplements will be prepared in feeding centres. De-worming will be done at the start of the intervention using mebendazole (500 mg). Demonstrations on porridge preparation and use of sprinkle and nutrition education focused on the importance of nutritious diet will be given to the primary caregivers on group basis at baseline.

Table 1: Micronutrient composition of sprinkles and CSB

|                  | Expt Gp 1:
Sprinkles (per 1
g sachet) | Expt Gp 2:
Sprinkles* (per 1
g sachet) | Expt Gp 3:
Sprinkles* (per 1
g sachet) | Comparator Gp
4: CSB ( 100g
dry wt.) |
|------------------|------------------------------------------------------|-------------------------------------------------------|-------------------------------------------------------|-----------------------------------------------------|
| Vit A (IU)       | -                                                    | 1250                                                  | 1250                                                  | 1300                                                |
| Vit E (mg)       | -                                                    | 6.0                                                   | 6.0                                                   | -                                                   |
| Vit C (mg)       | -                                                    | 30                                                    | 30                                                    | 30                                                  |
| Thiamine (mg)    | -                                                    | 0.5                                                   | 0.5                                                   | 0.1                                                 |
| Riboflavin (mg)  | -                                                    | 0.5                                                   | 0.5                                                   | 0.4                                                 |

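### The bioequivalence rule compares sprinkles with CSB without naming arms, although one sprinkles arm is zinc-free, and nothing in it asks whether zinc worked

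*Protocol*

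**What the plan says.** The Study design section lists three experimental groups that receive sprinkles, "zinc, zinc in multiple micronutrients and multiple micronutrients without zinc", and a CSB comparator. Table 1 gives 5 mg of zinc for sprinkles groups 1 and 2 and for CSB, and none for sprinkles group 3. The text above that table nevertheless speaks of "sprinkles meeting 100% RDA of zinc will be sourced from suppliers" without distinguishing the groups.

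The sample size section does separate the arms: "The estimated post-intervention prevalence of 20%, 10%, 20% and 50% for the reference, ZN, ZN in MMN and MMN without ZN groups respectively". The same section puts the national prevalence of zinc deficiency at 50%, so the zinc-free arm is expected not to improve.

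The decision rule is in Data analyses: "Bioequivalence of sprinkles to CSB will be drawn" when the shares of children with serum zinc below 9.9 µmol/L are within ±20, leaving out children with CRP above 10 mg/l. The protocol calls this "the basis to accept or reject the null hypothesis". It names no arms, does not say whether arms are pooled, and sets no condition on the zinc-free arm. General inter-group tests of zinc status (chi-square, t-test, ANOVA, ANCOVA) are planned in the same section but are not tied to the equivalence decision.

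**The concern.** There are two gaps.

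First, sprinkles in the rule could mean the two zinc-containing arms taken separately, all three arms pooled, or each of the three arms in turn. On the protocol's own planning rates these readings do not lead to the same answer. A primary rule whose outcome depends on an unstated choice of arms can be settled after the data are seen.

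Second, closeness to CSB shows equal zinc effect only if CSB had a zinc effect in this trial. Two arms in which zinc did nothing are also close to each other. Comparison with baseline does not settle this, because deworming and nutrition education are planned for the whole study and could move all arms together. The zinc-free arm is the one that separates a zinc effect from such a shared change, and the rule does not refer to it.

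**Working it through.** **Inputs.** Planned post-intervention rates: CSB 20%, zinc 10%, zinc in MMN 20%, MMN without zinc 50%; prevalence 50%; 67 children per arm; margin 20, described as "20 % as per the bioequivalence rule" (all from the sample size section). Three villages per arm (Randomization). The margin is read as percentage points. The protocol gives no intracluster correlation (ICC), so a range is assumed.

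**The plan's own figure.** The printed formula gives (1.64 + 1.28)² × 0.71² / (0.2 − 1.0)² = 8.526 × 0.504 / 0.64 = 6.7, not 67. That is a separate matter; 67 is taken here as the stated size.

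**Step 1: which arms, on the planned rates.**
- Pooled sprinkles: (10 + 20 + 50)/3 = 26.7% against 20%, a difference of 6.7 points. Exact binomial probability of meeting the rule: 99.3% on point estimates, 76.1% by a 90% interval.
- Zinc-free arm alone: 50 − 20 = 30 points. SE = √[(0.2×0.8 + 0.5×0.5)/67] = 0.0782, and Φ((0.20 − 0.30)/0.0782) = Φ(−1.28) ≈ 0.10. Exact: 10.5% on point estimates, 0.2% by a 90% interval.

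**Step 2: no zinc effect anywhere.** Let CSB and one zinc sprinkles arm both be at 50%. SE = √(2 × 0.25/67) = 0.0864.
- Point estimates: the arms may differ by up to 0.2 × 67 = 13.4, so 13 children. Normal approximation: 2Φ(0.2/0.0864) − 1 = 2Φ(2.315) − 1 = 0.979. Exact: 98.1%.
- 90% interval inside ±20: |d| must be below about 0.2 − 1.645 × 0.0864 = 0.058, so at most 3 children. Exact: 46.3%.
- 95% interval inside ±20: |d| must be below about 0.2 − 1.96 × 0.0864 = 0.031, so at most 2 children. Exact: 33.4%.

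If instead all arms, the zinc-free one included, fell to 20% through shared measures, the same three probabilities would be 99.6%, 79.0% and 64.8%.

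**Step 3: clustering, point rule, all arms at 50%.** Design effect = 1 + (67/3 − 1) × ICC.
- ICC 0.02: 1.427; SE = 0.0864 × √1.427 = 0.103; 2Φ(0.2/0.103) − 1 ≈ 0.95.
- ICC 0.05: 2.067; SE = 0.124; 2Φ(0.2/0.124) − 1 ≈ 0.89.

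Beta-binomial simulation with villages of 22, 22 and 23 children gives 95% and 90%.

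**Step 4: what the CSB versus zinc-free contrast can show (20% vs 50%).** Ignoring clustering, power at 67 per arm is 96%. In a village-level t test on 4 df, simulated power is:

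| Assumed ICC | Power |
|---|---|
| 0.01 | 73% |
| 0.02 | 66 to 67% |
| 0.05 | 52% |
| 0.10 | 39% |

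**The case against.** Several points on the other side stand.

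- A reader might infer that the protocol pools all sprinkles as one product. It does not say so. The Study design, Table 1 and the sample size section all keep the arms apart, and the description of sprinkles as meeting the zinc requirement allows the word to mean only the zinc-containing ones. The regression wording, "determine the contribution of sprinkles/CSB, dietary practices and SE status to nutrition status, morbidity patterns and" serum zinc, does not show pooling either. What can be said is that the comparisons are not named.
- A reader might also infer that a pooled comparison passes automatically, or that requiring all three arms to pass is impossible. Both go too far: the pooled version passes 76.1% of the time by a 90% interval, and the zinc-free arm passes 10.5% of the time on point estimates.
- It is not true that the zinc-free arm goes unused. The general inter-group tests include it, and serum zinc is measured before and after, so an unchanged 50% in every arm would be visible. None of these results bears on the equivalence conclusion, however.
- The protocol places significance at a 95% confidence interval, so the 98% figure belongs to one reading only. The range to quote is 33% to 98%.
- Comparison sets and gating are often left to a SAP. Here the protocol itself fixes the rule and makes it the basis of the decision, so the gap is in what is stated.
- Making success against the zinc-free arm a mandatory gate would be expensive. If the planned rates were exactly right, about a third to a half of trials would fail it at ICC 0.02 to 0.05. That argues for required reporting and graded interpretation, not a hard gate.

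**Conclusion.** The point holds in this form: the rule names no arms although one sprinkles arm is zinc-free, and it has no check that zinc worked. On the planned rates the choice of arms moves the difference from 6.7 to 30 points, from usually passing to usually failing. With every arm at 50%, equivalence would be declared with probability 98%, 46% or 33% depending on whether the rule uses point estimates, a 90% interval or a 95% interval. With clustering, the point-estimate figure is about 95% and 90% at ICC 0.02 and 0.05.

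These figures assume a margin in percentage points, 67 analysable children per arm (the CRP exclusion would lower this), and assumed ICCs; the interval figures ignore clustering. The documents do not support the stronger statements that the arms are pooled by plan or that the zinc-free arm is ignored throughout.

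**What to change.** In Data analyses:

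1. State the rule as two comparisons, each judged on its own: zinc sprinkles vs CSB, and zinc-in-MMN sprinkles vs CSB. Say whether the rule applies to point estimates or to an interval, and at what level.
2. Exclude the zinc-free arm from any sprinkles equivalence claim and from any pooled sprinkles term in the regressions.
3. Pre-specify the differences in percentage deficient between CSB and the zinc-free arm, and between each zinc arm and the zinc-free arm, with village-adjusted intervals, reported beside the equivalence result.
4. Interpret equivalence as equal zinc effect only where the CSB contrast supports CSB having worked. Otherwise report similarity without evidence of a zinc effect.

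This changes analysis wording only and needs no new data. The cost is in the conclusion: with three villages per arm the CSB contrast is underpowered at most plausible ICCs (Step 4 of the working), so some true equivalence results would carry the weaker statement.
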